### Statistical methods and data analysis

*Sample size*: sample size estimations suggest that 776 participants completed to week 8 are required.

The sample size was determined based on a minimum clinically relevant effect size (i.e. the difference in effect size between the TaU and PReDicT arms) which was set at 10% for the primary outcome (response at 8 weeks measured using the QIDS-SR-16). While there is no general agreement on minimum clinically relevant effect size, a review of the US Food and Drug Administration (FDA) data on antidepressant randomised controlled trials (RCTs) found that in RCTs of antidepressants versus placebo a minimum of 11% difference in response was significant and measurable [19]. In addition, during discussion with expert clinicians in the protocol development phase an effect size of less than 10% was considered to be clinically non-significant. The baseline response rate in the TaU group was estimated, based on data from a pilot study [11], at 40%. Adding the minimum clinically relevant effect of guided treatment of 10% to this value results in a response rate of 50% in the PReDicT-guided arm. Setting alpha at 0.05 and power at 80% indicates that a total sample size of 776 participants with primary outcome data (388 per group) would be required to detect the specified minimum clinically relevant difference of 10%. The expected attrition rate across the first 8 weeks of the trial, based on data from the pilot study, is 33%. Participants withdrawn from the study will not be replaced (that is an intention-to-treat analysis will be performed), thus 1158 participants will be enrolled to ensure that 776 participants complete the study.

*Analysis of primary objective*: logistic regression will be performed to explore treatment effects on the rates of response using an intention-to-treat approach.

*Analysis of exploratory objectives*: for the following outcomes which are analysed at week 8 of the study: MADRS, GAD-7, DSST scores, SAS-SR (screener version) and QIDS-SR-16 (including anxiety and depression items score), linear regression will be performed to quantify treatment effects with a baseline measure included as a covariate [20].

For other exploratory outcome measures, including SAS-SR (screener version) and QIDS-SR-16, which will be followed up monthly over the period of 1 year, multilevel modelling will be conducted to quantify treatment effects with ‘participant’ as a level-2 unit, treatment status and treatment × time interactions. Baseline measurement will be included in the multilevel models as a covariate [21].

For all regression modelling, age, gender, and baseline depression score will be included as covariates and country influence on treatment effect estimates will also be adjusted [22, 23]. Outcome missing value patterns will be examined and the influence of baseline measures and treatment allocation on missingness will investigated to inform multiple imputation procedure under the missing-at-random assumption.

An exploratory sensitivity analysis will test the effect of modifying the algorithm after 110 patients have completed the study.

*Analysis of health economic objectives*: the main health economic analysis will include: (1) a detailed patient-level cost analysis of health, social care and other broader societal costs for both the PReDicT and TaU arms of the study and (2) an incremental within-trial economic evaluation comparing the PReDicT arm and the TaU arm of the study in terms of their costs and outcomes over a 6-month follow-up period (week 0 to week 24). An optional health economic analysis may be also conducted over the full 12-month study follow-up period.

*Analysis of acceptability and implementation objectives*: acceptability questionnaires will be reported using descriptive statistics. Free text comments will be analysed thematically. Questionnaire and demographic data will be used to guide sampling for semi-structured interviews performed on a subsample of patients and clinicians.

Both the questionnaire and interview data will be used to develop an inductive analysis of the value and implementation of the PReDicT Test.

*Analysis of safety objectives*: safety data will be reported using descriptive statistics.

*Interim analysis*: an interim analysis will be performed when approximately 300 participants have been recruited. The interim analysis will assess recruitment rates within each country, adherence to the protocol and safety in terms of adverse events and device deficiencies in the two study arms. The interim analysis will also assess the effect size of the difference between the PReDicT arm and TaU arm on the primary outcome in order to assess the underlying assumptions of the power analysis and, if necessary, suggest an increased target recruitment figure. The interim analysis will be carried out and assessed by an independent Data Monitoring Committee (i.e. who are not authors of this paper or members of the study team) who will then, if necessary, make recommendations to the sponsor about whether alterations to the study protocol are required to meet the study objectives. The Data Monitoring Committee will consist of an experienced psychiatric trialist, an additional experienced trialist and a biostatistician.^5^ As all medications used in the study are licensed antidepressants, no formal stopping criteria will be used.

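### The interim may raise recruitment on the observed arm difference, although the sample size rests on a fixed 10-point minimum relevant difference and the interim estimate carries about ±14 points

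*Protocol article*

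**What the plan says.** Both statements are in the protocol article, under Statistical methods and data analysis.

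- **Sample size.** The trial is sized on a minimum clinically relevant difference in week-8 response of 10 percentage points. The article reports that, among the expert clinicians consulted, "an effect size of less than 10% was considered to be clinically non-significant". A pilot-based response of 40% under Treatment as Usual plus 10 points "results in a response rate of 50% in the PReDicT-guided arm". Alpha 0.05 and 80% power give 776 participants with outcome data (388 per arm). With 33% attrition, "thus 1158 participants will be enrolled to ensure that 776 participants complete the study".
- **Interim analysis.** When about 300 participants have been recruited, an independent Data Monitoring Committee reviews recruitment, adherence and safety. In addition, "The interim analysis will also assess the effect size of the difference between the PReDicT arm and TaU arm on the primary outcome", so that the power assumptions can be examined and the committee can, "if necessary, suggest an increased target recruitment figure". There are no formal stopping criteria. No formula, cap or error-controlling method is given for the increase.

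The Randomisation section adds that the first 110 participants are allocated 1:10 to PReDicT and Treatment as Usual, with a 1:1 ratio to be reached over the whole trial.

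**The concern.** A minimum clinically relevant difference is a judgement about what is worth detecting. Interim data cannot show it to be mistaken. The sample-size assumptions that data can correct are the response level and the attrition rate, and the Interim analysis paragraph names neither. It names the between-arm difference.

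If a smaller observed difference leads to more recruitment, the trial is being powered for effects its own Sample size paragraph sets aside. The prompt for doing so would be an imprecise estimate. An increase that depends on the unblinded difference can also disturb the type I error of the final test unless the method allows for it. At stake are a possibly large and unnecessary extension of recruitment and a small loss of error control.

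**Working it through.** **1. Reproduce the plan's figure.** Inputs from the Sample size paragraph: 40% versus 50%, alpha 0.05 (two-sided inferred, because it reproduces the stated total) and power 80%. With p̄ the mean of the two rates and d their difference, the number per arm is

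n = [1.960·√(2p̄(1−p̄)) + 0.842·√(p₁(1−p₁)+p₂(1−p₂))]² / d²

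= [1.960·√0.495 + 0.842·√0.49]² / 0.01 ≈ 387.3, so 388 per arm and 776 in total. This matches. Enrolment: 776/0.67 = 1,158.2, against 1,158 stated.

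**2. What can raise the requirement?** The same formula gives:

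| Rates | Difference | Completers | Enrolled at 33% attrition |
|---|---|---|---|
| 40% v 50% | 10 points | 776 | 1,158 |
| 45% v 55% (largest variance for 10 points) | 10 points | 784 | about 1,170 |
| 40% v 48% | 8 points | 1,208 | 1,803 |
| 40% v 45% | 5 points | 3,068 | 4,580 |

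With 10 points fixed, the response rates can add at most 784 − 776 = 8 completers. Attrition apart, any material increase needs a difference below 10 points. The last two rows are illustrations; the article does not say the size would be recalculated in this way.

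**3. How precise is the interim difference?** 300 × 0.67 = 201 with week-8 data, assuming 33% attrition and that all 300 have reached week 8. The half-width is 1.96·√(0.25/n_P + 0.24/n_T).

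- Equal arms, 100.5 each: SE 6.98 points, ±13.7.
- First 110 split 10:100 and the next 190 split 95:95, giving 105:195 recruited and about 70:131 completers: SE 7.34 points, ±14.4.
- Allocation catching up evenly over the trial, giving 113:187 recruited and about 76:125 completers: ±14.2.
- Outer cases: ±11.2 to 11.8 if all 300 had outcomes; ±17.2 if the first 110 were left out.

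**4. How often would it mislead?** With a true difference of 10 points, P(observed below 5) = Φ(−5/6.98) ≈ 0.24 to Φ(−5/7.34) ≈ 0.25. An observed difference at or below zero occurs in about 8–9% of trials.

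**5. Type I error if the final test were unadjusted.** Simulation with 40% response in both arms, an interim of 70 v 131 or 100 v 101 completers, an increase-only recalculation at the observed difference, caps of 1.5, 2 or 4 times 776, and an ordinary z-test at the end (400,000 trials per scenario):

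- size fixed at 776: about 5.1%
- increase only when the difference favours PReDicT: 5.3–5.6%
- increase on any difference under about 10 points, in either direction: 5.5–6.0%

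A second set of rules, including re-powering to 80% conditional power, gave 5.17–5.98%. Overall the range is about 5.2–6.0%.

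**6. What the increase buys.** Under the step 5 recalculation rules, power for a true 5-point effect rises from 29% to 35–62%. That is an effect below the plan's own threshold.

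**The case against.** The article condenses a fuller protocol. The committee is independent, includes a biostatistician and only makes recommendations. No interim efficacy test or early stop is planned, so no alpha is spent on an interim rejection. A cap, a rule and alpha handling may sit in the full protocol, the analysis plan, the committee's charter or the footnote on the committee, whose text is not shown. All of this stands. It limits the error-control point to saying that none is stated here.

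Four stronger readings are tempting, and the document does not support them:

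- **That the final test will be run at an unadjusted 0.05 after a size change.** The 0.05 appears in the sample-size calculation. The primary analysis is described only as an intention-to-treat logistic regression, with nothing on how a size change would be handled.
- **That a large increase would often be triggered by chance.** This needs a mechanical re-powering rule, and the article has none. A committee faced with ±14 points might well decline to act. That an unbiased estimate falls below a true value of 10 about half the time is no defect in itself.
- **That the sponsor could work back from a new target to the interim effect.** This needs a known formula, and the committee also weighs recruitment, adherence and safety.
- **That the 1:10 start is what makes the estimate imprecise.** It moves the half-width only from 13.7 to 14.4 points.

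It is also fair to say that the article admits there is no general agreement on a minimum relevant effect. It nonetheless adopts 10 points and sizes the trial on it. What remains is a stated use of the arm difference that conflicts with the stated basis of the sample size. An alpha adjustment documented elsewhere would not remove that conflict.

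**Conclusion.** The point holds as an inconsistency between two paragraphs of the same section. The Interim analysis paragraph lets the observed difference bear on recruitment. The Sample size paragraph leaves no role for a difference below 10 points, and with 10 points fixed the response rates can move the requirement only from 776 to 784. The quantity to be used has a 95% half-width of about 14 points, wider than the target difference. This assumes 33% attrition and complete week-8 follow-up of all 300; it would be wider if recent recruits had no outcome yet.

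The error-rate consequence is modest and conditional: about 5.2–6.0% two-sided against a nominal 5% (about 5.1% in the same simulations at fixed size), and only if the final test is left unadjusted. The change is worth making before the interim, but the matter does not threaten the trial's validity: should-fix rather than must-fix.

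**What to change.** Reword the Interim analysis paragraph and the committee's brief so that:

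1. the 10-point difference stays fixed;
2. the arm difference on the primary outcome is removed from the sample-size reassessment;
3. any increase is based on the week-8 response rate pooled over arms, without treatment labels, and on observed attrition, with enrolment equal to required completers divided by (1 − attrition).

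Because the response rate can add at most 8 completers, attrition will in practice drive any change.

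If the sponsor wishes to keep the arm difference, a cap and an alpha-preserving rule (a combination test or a conditional-power zone) should be fixed in writing before the interim data are seen. The reason for powering below 10 points should then be reconciled with the Sample size paragraph. If such a rule already exists elsewhere, the article should refer to it.

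The cost is one paragraph and no additional patients. What is lost is the option of an effect-driven increase, which the plan's own relevance threshold does not support.

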## Discussion

This trial provides a rigorous assessment of the clinical effectiveness as well as economic value and overall acceptability of deploying the PReDicT Test to guide antidepressant treatment of depressed patients. If successful, the trial will provide evidence to support a significant alteration in the standard treatment of depression. Specifically, it will suggest a method by which the process of identifying and initiating effective treatments can be substantially condensed relative to current standard practice [5]. By specifying non-responsive patients from a neuropsychological perspective, drawbacks of other studies of early switching of antidepressants might be overcome [24]. From the perspective of a depressed patient, a rational system which is able to more rapidly identify an effective treatment for their illness may well enhance confidence in, and improve adherence to, treatment plans. Conceivably, the ability to personalise treatment may also enhance the risk/benefit assessment of antidepressant use which has been questioned in a recent study which pooled data from clinical trials of the non-personalised use of antidepressants [25].

Clearly, the response of patients to antidepressant treatment is variable, with evidence from treatment trials indicating that separation from placebo can be detected at the group level after 1–2 weeks of treatment [26] and side effects commonly occurring early in the course of treatment. The PReDicT Test is, therefore, expected to be one of a number of potential sources of information that clinicians may draw on when making treatment decisions, rather than the sole arbiter of that decision. This is reflected in the design of the current trial in which clinicians are informed of the result of the PReDicT Test but are not required to use this information in their treatment decision if, for example, the patient has clearly responded or developed side effects.

The PReDicT Test used in this trial has been developed as part of a translational research programme which investigates treatment mechanism in depression, largely utilising non-clinical human models of cognition in controlled laboratory settings, [12]. This trial, therefore, also provides an important opportunity to test the potential benefits of using recent advances in cognitive neuroscience to improve patient care in mental health.

### Trial status

Recruitment started in the UK in July 2016. Recruitment in other countries is expected to start in late 2016/early 2017.

## Appendix 1

**Table 2 Tab2:** Time and events table – clinical phase activities

	Visit 1: screening and PReDicT #1	Treatment start date	PReDicT #2	Visit 2 (if required)	Change of dose start date^a^ (if required)	PReDicT #3 (if required)	Visit 3 (if required)	Change of medication start date^b^ (if required)	Visit 4^c^
Requirements for timing of visit/event	Within 7 days of initial consultation	Day 0	≥7 days after day 0			≥ 7 days after changed dose			≥ 8–10 weeks after day 0
Preferred timing		Day 0	7–9 days after day 0	0–1 day after PReDicT #2	0–1 day after visit 2	7–9 days after changed dose	0–1 day after PReDicT #3	0–1 day after visit 3	8 weeks after day 0
Informed consent	X								
Entry criteria check	X								
Change in antidepressant (AD) medication agreed				X^a^			X^b^		
Review of concomitant medication									X
Review of AEs, ADEs and device deficiencies	X								X
Assessments									
PReDicT Test	X		X			X^a^			
QIDS-SR-16	X^d^	Completed weekly, starting 7 days after day 0							X^d^
Randomisation	X								
EQ-5D-5 L	X								X
HEQ	X								X
OxCAP-MH (UK and Germany only)	X								X
SAS-SR (screener version)	X								X
GAD-7	X								X
DSST	X								X
MADRS	X								X
Patient Acceptability Questionnaire									X

^a^If PReDicT #2 outcome = non-response, physician decides if antidepressant will be changed. PReDicT #3 will be completed

^b^If PReDicT #3 outcome = non-response physician decides if antidepressant will be changed

^c^Participants who withdraw will be invited to complete (in order of preference): visit 4 (at 8-week time point); visit 4 online questionnaires (from home at 8-week time point); Patient Acceptability Questionnaire (immediately); no additional data

^d^QIDS-SR-16 is included in the PReDicT Test

*AE* adverse event, *ADE* Adeverse Device Event, *EQ-5D-5 L* 5-dimensional, 5-level EuroQoL health-related quality of life questionnaire, *DSST* Digit Symbol Substitution Test*, GAD-7* Generalised Anxiety Disorder Questionnaire, 7-item version, *HEQ* Health Economics Questionnaire, *OxCAP-MH* Oxford CAPabilities questionnaire-Mental Health, *MADRS* Montgomery-Åsberg Depression Rating Scale, *QIDS* Quick Inventory of Depressive Symptomatology – Self Report

## Appendix 2

**Table 3 Tab3:** Time and events table – follow-up phase activities

Online activity	Follow-up #1	Follow-up #2	Follow-up #3	Follow-up #4	Follow-up #5	Follow-up #6	Follow-up #7	Follow-up #8	Follow-up #9	Follow-up #10
Timing of activity^a^	Week 12 i.e. 4 weeks after visit 4	Week 16	Week 20	Week 24	Week 28	Week 32	Week 36	Week 40	Week 44	Week 48
QIDS-SR-16	X	X	X	X	X	X	X	X	X	X
EQ-5D-5 L	X	X	X	X	X	X	X	X	X	X
HEQ	X	X	X	X	X	X	X	X	X	X
OxCAP-MH (UK and Germany only)				X						X
SAS-SR (screener version)				X						X

^a^Data can be captured any time up to the due date of the next follow-up

*EQ-5D-5 L* 5-dimensional, 5-level EuroQoL health-related quality of life questionnaire, *HEQ* Health Economics Questionnaire, *OxCAP-MH* Oxford CAPabilities questionnaire-Mental Health, *MADRS* Montgomery-Åsberg Depression Rating Scale,*QIDS* Quick Inventory of Depressive Symptomatology – Self Report, *SAS-SR* Social Adjustment Scale, self-report version

## Abbreviations

CE: Conformité Européene
DSST: Digit Symbol Substitution Test
ePRO: Electronic patient-reported outcomes
EQ-5D-5 L: 5-dimensional, 5-level EuroQoL health-related quality of life questionnaire
GAD-7: Generalised Anxiety Disorder Questionnaire, 7-item version
HEQ: Health Economics Questionnaire
MADRS: Montgomery-Åsberg Depression Rating Scale
OxCAP-MH: Oxford CAPabilities questionnaire-Mental Health
PReDicT Test: Predicting Response to Depression Treatment Test
QIDS-SR-16: Quick Inventory of Depressive Symptomatology – Self Report, 16 Item Version
SAS-SR (screener version): Social Adjustment Scale – Self-Report (screener version)
SSRI: Selective serotonin reuptake inhibitor
TaU: Treatment as Usual
UK: United Kingdom.
